[figure not shown]

[figure not shown]

# BACKGROUND AND RATIONALE

One important target of the Millennium Development Goals (MDG) is “to halve, between 1990 and 2015, the proportion of people who suffer from hunger”. The prevalence of underweight children under-five years of age is a monitoring parameter of that target achievement . Improving child nutrition has considerable effects on children survival rates, quality of life, and individual and society development. The recent Lancet series on maternal and child under-nutrition estimated that stunting, severe wasting, and intrauterine growth restriction were together responsible for 2.2 million deaths and 21% of disability adjusted life-years (DALYs) in under-five years children . 156 million children in developing countries don’t reach their optimal development and chronic malnutrition is a major risk factor of cognitive, intellectual, and socio-emotional deficits . Under-nutrition can affect cognitive development by causing direct structural damage to the brain and by impairing infant motor development and exploratory behaviours . In the long-term, it bears under-nutrition are consequences in adult human capital and economic productivity . Moreover, better nutrition is also central for the achievement of the other MDGs, as emphasized by the SCN and the World Bank recently .

However, since the 90’s, the situation has little improved. The rate of the underweight children in developing countries decreased from 33% in 1990 to 28% in 2003. The situation is more alarming in Sub Saharan Africa, where a very slow evolution is noted . More pessimistic estimates even forecasted a rise of underweight children, from 24.0% in 1990 to 26.8% in 2015, in Africa . So that the international community recognizes today that achieving the MDGs will not be possible if the current trends (1990-2003) are maintained .

The efficacy of a number of interventions to address child under-nutrition has been thoroughly demonstrated. Those interventions include: promotion of breastfeeding (individual and group counselling); behaviour change communication for improved complementary feeding; zinc supplementation; zinc in management of diarrhoea; vitamin A fortification or supplementation; hand washing or hygienic; and treatment of severe acute malnutrition following WHO protocol . If implemented at sufficient scale, those interventions could reduce mortality between birth and 36 months by about a quarter. The development and spreading of an integrated management of childhood illnesses (IMCI) was also an important step towards better child health .

However, a major bottleneck in fighting malnutrition is precisely the incomplete and/or dysfunctional implementation of those interventions, resulting in missed opportunities of good quality management . Hindering factors vary in size, nature, and by settings, but three important dimensions can be identified:

**1. Communicational dimension:** An effective and comprehensive communication between health workers and caretakers is an essential step for an adequate management of child nutrition issues. However, health workers are often lacking that essential skill , resulting in poor efficiency of growth promotion programmes. In contrast, nutrition counselling training can change health worker behaviours and improve caregiver knowledge acquisition and child growth. However, evidence currently available has been mainly collected in urban settings with qualified health professionals. There is an obvious need of developing and evaluating the impact of such counselling training in nurses who bear the essential responsibility of providing most of the primary health care in developing country.

**2. Functional dimension:** A variety of characteristics of health service management (e.g. lack of incentives for health workers to engage in nutrition counselling; absence of monitoring of services quality; separation of curative and preventive services) hampers sustained nutrition intervention . Des-integration of IMCI is a striking example. Although part of the IMCI, nutrition is a dimension of child health often neglected by health workers . Moreover, the whole IMCI package is insufficiently implemented, most often due to the low utilization rate of health services by the population and the generally poor performance of health staff in rural settings . There is a need for innovative strategies leading to an effective implementation of all components of the IMCI in primary health care.

**3. Structural dimension:** The management of severe acute malnutrition has been well formalized in WHO protocols , and there is good evidence that where these protocols were available and sufficient attention was paid to the quality of care, case-fatality rates substantially decreased . However, the application of these protocols required numerous trained staff and a sufficient inpatient bed capacity. Moreover, in rural settings, hospital-based management results in late presentation of cases and high opportunity costs for caretakers, as well as serious risks of cross infection . Finally, the protocols are based on the utilization of treatments (F-75, F-100) which are expensive and not readily available in poor settings. Therefore, means of managing acute severe malnutrition in rural health districts where a centralized and costly, externally supported, approach is not suitable must be developed. Community-based approached are promising alternatives . However important questions arise when considering the scaling up of such program in non-emergency contexts: how can the high price of commodities are managed in the frame of limited budget allocated to health services? What is the best way to integrate programmes with health services? How can programmes be implemented with less qualified staff?

**Nutrition and health services in Houndé district.**

**Baseline assessment (April-June 2008)**

**Data collection**

**- Interviews of health workers (n=27), direct observations of the management of child illnesses (n=141) and exit interviews of caregivers (n=215) were carried out in the 27 primary health centres.**

**- Household survey (representative sample of 2164 households including 3912 children).**

**Population of under five children in the district40.000**

**Malnutrition rates in the district:**

- 16.4 % of the under-5 children are wasted and 38.7% are stunted (35.7% are underweight)
- 39% of the children ages 0-59 months had been sick during the previous two weeks

**Feeding practice**

*Breastfeeding*

-Only 47.8% of mothers have given the colostrum to their baby; 42.8% have given something to drink in the tree first days after delivery (water=64.8%). The average duration of the breastfeeding was of 15.9 ±5 months. The most frequent reason for early discontinuation of breastfeeding was: pregnancy (37.5%).

*Complementary feeding practices:*

- 39.1% of infants received complementary food before 6 months. In most of the cases the complement food given was simple millet porridge (85.5%).

-The average age to associate children to the family plate was 9.7±3.8 month.

- The average score of variety in the last 24 hours, on 9 food groups was 2.0±1.17 with a median of 2.0.

**Communicational dimension of health services**

*Curative consultation*

- 62.5% of the caregivers consulting for a sick child didn’t receive nutritional counselling; 83.0% didn’t receive the advice of increasing the fluids in case of diarrhoea; 55.3% were not advised to continue feeding the sick child.

*Reproductive health*

- 67.6% of pregnant women don’t receive food practices counselling; and 62.3% deceased her food intake in quantity, 31.2% in variety. 13.7% are declared that there is food which was forbidden them during the pregnancy. 69.8 of pregnant don’t receive any counselling on exclusive breastfeeding; 71.2% any counselling on breastfeeding practice thought the health facilities.
- Only 24.2% of interviewers had received counselling on complementary feeding though health facilities, 95.4% of them considering the advice useful

**Functional dimension of health services**

**-**The majority of facilities (85%) offer growth promotion activities during immunization sessions, but participation rates remain low (366 children in 2007).

**-** 70.6% of sick children were not weighted; 99.1% didn’t have their length/height measured; health workers failed to ask about diet modifications in 75% of the cases.

**-** There is no follow-up file for malnourished children

- 29.2% of the newborns were not weighted

**Structural dimension of health services**

-The majority of the centres (96%) have only one baby balance, but only 6 centres (22%) had length/height scale which was moreover rarely used.

-There is no functional Nutrition Rehabilitation Centre (NRC) in the district. The cases of severe malnutrition must be transferred at Bobo (more than 100km of the district hospital).

We propose to improve child nutrition in the Houndé district by an intervention which addresses those three essential dimensions of health services. During infancy and early childhood, contact with health services, particularly for curative care, is perhaps the single most common source of institutional contact between families and public health sectors services. Moreover, the credibility that health care providers are typically accorded in many social settings suggests that nutrition advice delivered by practitioners may be particularly persuasive .

First, the communicational dimension will be improved through developing a patient-centreedness approach. The patient-centreedness model developed by Stewart et al will be the guiding line of the intervention. This model takes into account six interconnecting components (figure 1): 1) Exploring both disease and illness experience, 2) understanding the whole person; 3) funding common ground regarding management; 4) incorporating prevention and health promotion; 5) enhancing the doctor-patient relationship; 6) being realistic about personal limitations and issues such as the availability of time and resources.

Second, the functional dimension will be addressed

1) by adapting the IMCI strategy to the local environment and making it the effective pivotal tool of all under-five consultations . Much has been learned from disease-specific control programs in the past 15 years. The current challenge is to apply the lessons from these programs to strategies that promote coordination and greater integration of activities in order to improve the prevention and management of childhood illness, including malnutrition. The IMCI strategy combines improved management of childhood illness with aspects of nutrition, immunization, and other important factors influencing child health, including maternal health.

2) Moreover, if one looks at the prevalence of malnutrition and the accumulation of the deficit in linear growth, it is clear that the first 18 months of life are a very vulnerable period for changes in feeding habits. Maternal nutrition during pregnancy and lactating, impacts on child growth. We know that efficient breastfeeding protects children from diseases and provides them with the most suitable food intake. Another period of risk is the weaning period where less suitable food combinations are often given to the children. In contradiction to these observations, growth promotion activities of the health services have been so far spread over the 5 first years of life, with discouraging results both in terms of follow-up rates and outcomes . We proposed to reorganize health services in order to maximize contacts between caretakers and caregivers during the critical period and support mothers in their effort to provide the best possible food to their offspring. The activities to improve child growth and development will be essentially promotional and preventive and based on regular contacts. Growth promotion activities will begin during pregnancy, and will be combined to immunization sessions and child sick consultations after birth.

Lastly, we will develop an integrated strategy of community-based rehabilitation of severe malnourished cases, and children play session to all services provided to children.

**Figure 1: The patient-centreed clinical method: six interactive components**

**2: Understanding the whole person**

Take into account the multiple aspects of the child life.

Developmental history;

Life cycle issue and feeding;

The multiple contexts in which they live including the ecosystem.

**1: Exploring child both disease and illness experience**

-Explore the caregiver feeling and idea about her child disease

-How the child illness is impacting on his functioning

What her expect from the physician

Proximal context

Distal context

Disease

Illness

History and

Physical examination

Feeling

Ideas

Function

Expectation

The children Person

**3. Funding common ground**

Defining the problem

Establishing the goals of treatment and/ or management

Identifying the roles to be assumed by the caregiver and provider

**4. Incorporating prevention and health promotion**

Counseling on feeding practice adapted to child age and illness experience,

Hygiene

Vaccination

**6. Being realistic**

About time

Improving teambuilding and teamwork

Rationalize the available resources

Mutual decision

1. **Enhancing the caregivers Provider relationship**

Each contact with the caregiver will be use to build and improve the caregiver-physician relationship by including compassion, trust, a sharing of power and healing.

Source: Moria Stewart, et al., *Patient-Centreed Medicine Transforming The Clinical Method.* PATIENT-CENTREED CARE, ed. Moria Stewart, Judith Belle Brown, and T.R. Freeman. 2003.

# OBJECTIVES

***Goals:***

To improve the nutritional status and care quality of under-5 children in Houndé district, by a three-fold intervention in primary health care services: enhancement of patient-centeredness, actual implantation of the IMCI package and community-based rehabilitation of Severe Acute Malnourished children, using local RUTF.

***Targets***

*Outcomes:*

- To reduce morbidity rate in under five children

- To reduce wasting rate in consulting children by 50% (from 16% to 8%)

- To reduce the annual incidence of severe malnutrition by 50%

- To reduce the cost of severe malnutrition care

-*Processes:*

- To improve communication and management skills of primary health workers, particularly in the domain of nutrition, by 100% (all mothers should be advised about exclusive breastfeeding and complementary feeding, instead of the current 24%; all sick children should have their weight and length/height measured at any consultation; all mothers of sick children should be asked and advised about feeding practices)

- To improve knowledge and feeding practices of caretakers by 50% (75% of the mothers will give the colostrums to the newborn; 60% of the mothers will practice exclusive breastfeeding)

- To manage cases of severe acute malnutrition in each health facilities

- To manage cases of severe acute malnutrition in line with international recommendations of good practice.

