## Population and sample size

This study concerns all the health workers in the primary health facilities of the Houndé district and the children from 0 to 24 months as well as their mother or caretakers. The intervention unit is the health center and the population living in its catchment area, i.e. health centers will be randomized.

For the evaluation as well of the efficiency as of the impact of this intervention, the statistical unit will be consisted the center of health and its population of cover. On the level of each statistical unit, three types of samples will be necessary in comparison with the study populations:

- Health workers

A random sample of one health worker will be made by center.

*Inclusion criteria*: Personnel of health having at least one year of activity in the center.

Caregivers

Insofar as several outcomes used to compare the two groups of mother, the principal outcome used to compare the two groups, will be the proportion of caregivers having a good score of Knowledge on adequate breastfeeding and complementary feeding practices.

Several hypothesis have been considered to estimate the sample size. The reference method for the sample size calculation is the paper of Hayes et al for cluster design; we used equation N°4 of this paper

C=number of pairs=6 in our case Km = intracluster correlation coefficient; in the case of paired groups, 0, 25 is used as conservatory value.

= proportion of caregivers with a good score of Knowledge in the control group

= proportion of caregivers with a good score of Knowledge in the intervention group

n=sample size by cluster

The value of C being known in our case, we deduced from this equation, the values of n, according to several assumptions on the rate of caregivers with good knowledge and practices on breastfeeding and complementary feeding and according to two levels of power 1-β=0,80 or 0,90. This is shown in the table below.

**Estimate of the number of caregivers** necessary to compare the two groups

| = 0,25 | α=0,05  1-β=0,80 | α=0,05  1-β=0,90 |
| --- | --- | --- |
|  | n=15 | n=50 |
|  | n=33 | n=95 |
|  | n=11 | 20 |

By taking a maximum power, a sample of 95 women per cluster will be necessary, which is 1140 women in total.

*Inclusion criteria*: all women of childbearing age having a child into care from 0 to 59 months and living in the health center catchment area for at least one year at the time of the survey.

Children from 0 to 24 months

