Taking into account the duration of the intervention a notable change on the child nutritional status could be measured at the level of wasting; which is relevant to measure in children 0 to 24 months. The primary outcome, to compare the two groups will be the proportion of wasted children that is to say the proportion of children with weight for height Z score ≤ -2. According to the baseline data, this proportion was 16.4 on average in the district. The same equation cited above was used to estimate the number of required children. We considered the hypothesis that, after the intervention, the proportion of wasted children would decrease from 16.4% to 10% in the intervention area. Considering two levels of power the numbers of required children is summarized in the table below.

Table IV: Estimate of the number of children necessary to compare the two groups

| = 0,25 | α=0,05  1-β=0,80 | α=0,05  1-β=0,90 |
| --- | --- | --- |
|  | n=180 | n=650 |

We also considered other values of:

| = 0,20 | α=0,05  1-β=0,80 | α=0,05  1-β=0,90 |
| --- | --- | --- |
|  | n=115 | n=200 |

| = 0,30 | α=0,05  1-β=0,80 | α=0,05  1-β=0,90 |
| --- | --- | --- |
|  | n=800 | n=5000 |

We finally kept our first hypothesis with = 0.25, 1-β = 0.80 which gives n = 180 (180 children per cluster).

I*nclusion criteria*: all children 0 to 24 months whose parents residing in the health center catchment area for at least one year at the time of the survey.

The selection of women and children will be in population and randomly. In contrast, the number of children required (180 by cluster) being greater than the number of women (95 per cluster), and to be more operational, we will choose to include in the study women of childbearing age with at least a child under 24 months. This will allow us to select our two populations at the same time.

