## Data collection:

Data will be collected by trained field workers who are not involved in the delivery of the intervention:

-Interview through a structured questionnaire before, 3 month after the training of health workers and at the end of the intervention to test their knowledge on child nutrition counselling;

- Direct observation of five sick children consultation, and five preventive consultation with each provider, at the same time (before training, 3 month and 12 after the training) to test health providers’ skills in child health and nutrition management, their practice of communication and attitudes with regard to the children and their parents, the aspects related to the context of the meeting (latency, duration of the consultation…) and the quality of care provided.

- Exit interview with caregivers to measure their satisfaction as regards the services offered (growth promotion Program, curative care, communication and relation between health workers, nutrition counseling, malnutrition cases management), their practical knowledge, aptitudes as regards pregnant woman and the young child feeding practices, adapted care, family planning, etc

- At 3, 9 and 12 months, morbidity, health facilities use, anthropometry assessment, breastfeeding/complementary feeding practices reported on at 24-hour dietary recall and child psychosocial development assessment will be made.

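### The colostrum target and other birth-time practices have no birth window; in the sample the protocol defines, a 12-month survey would dilute the effect on them by about half

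*Protocol*

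**What the plan says.** - **Target.** Under Objectives, Targets (processes), the protocol aims that "75% of the mothers will give the colostrums to the newborn; 60% of the mothers will practice exclusive breastfeeding". These figures illustrate an intended 50% improvement in caretakers' knowledge and feeding practices. No denominator, birth window or measurement time is attached.
- **Baseline.** The Feeding practice part of the baseline box reports: "Only 47.8% of mothers have given the colostrum to their baby".
- **Sample.** Section 3.5 first defines the caregiver sample as "all women of childbearing age having a child into care from 0 to 59 months". It then replaces this for operational reasons: "we will choose to include in the study women of childbearing age with at least a child under 24 months". Eligibility is judged at the time of the survey and selection is random in the population.
- **Outcome.** Section 3.6 lists implementation of recommended feeding practices as a secondary outcome. Table 3, which sets out those practices, includes starting breastfeeding within about an hour of birth and giving no prelacteal feeds.
- **Timing.** Section 3.7 places morbidity, anthropometry and feeding assessments at 3, 9 and 12 months without naming the starting point. The wording "before training, 3 month and 12 after the training" in the same section concerns observation of consultations, not a survey of mothers.
- **Exposure.** The Background and section 3.3.3 start the new contacts during pregnancy, from the first antenatal visit.

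**The concern.** Colostrum, early initiation and prelacteal feeding happen once, at or just after birth. A mother who delivered before the health workers were trained cannot have had those practices changed by the training. If her answer is pooled with those of mothers who delivered afterwards, she adds a fixed baseline response to both arms and pulls the difference towards zero.

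Two things are at stake. A real and substantial change in birth-time practice could be reported as a modest one, or missed with only six pairs of centres. And the 75% target, read on the whole sample, would ask for more than near-complete uptake among exposed mothers could deliver.

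**Working it through.** **Inputs.** From the protocol: baseline 47.8%; target 75%; child under 24 months (main case) or 0-59 months (replaced criterion); 6 pairs; between-cluster coefficient k = 0.25; 180 children per cluster, with their mothers selected at the same time; 95 women per cluster. Assumed: uniform child ages, a survey 12 months after training, exposure from the date of training, and controls staying at 47.8%.

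**1. The plan's own figure.** A 50% relative improvement on 47.8% is 47.8 × 1.5 = 71.7%. Closing half the gap to 100% gives 47.8 + 0.5 × 52.2 = 73.9%. Neither is 75%; a baseline rounded to 50% would give it (50 × 1.5 = 75).

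**2. Share of births that can respond.** e = 12/24 = 50%. Under the 0-59 month criterion, e = 12/60 = 20%.

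**3. Dilution.** If exposed mothers reach 75%, the sample shows 0.5 × 75 + 0.5 × 47.8 = 61.4%. The observed rise is 61.4 − 47.8 = 13.6 points, against a true 75 − 47.8 = 27.2.

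**4. Ceiling.** With 100% colostrum among exposed mothers, ceiling = e × 100 + (1 − e) × 47.8.

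| Survey and window | e | Ceiling |
|---|---|---|
| 12 months, under 24 months | 50% | 73.9% |
| 9 months, under 24 months | 37.5% | 67.4% |
| 3 months, under 24 months | 12.5% | 54.3% |
| 12 months, 0-59 months | 20% | 58.2% |

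The 3- and 9-month rows apply only if those rounds are also counted from training.

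**5. Rate needed among exposed mothers.** For 75% overall: (75 − 0.5 × 47.8)/0.5 = 102.2%. For 71.7% overall: (71.7 − 23.9)/0.5 = 95.6%. If 60% of index children were born after the start, 75% would need (75 − 0.4 × 47.8)/0.6 = 93.1%.

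**6. Sensitivity of the 73.9%.** Break-even for 75% is e = (75 − 47.8)/(100 − 47.8) = 52.1%, or 12.5 months of a 24-month window.
- Survey at 13 months: 76.1%.
- Women report on the youngest child, and 8% or 10% of those with a child aged 12-24 months have a newer baby: 75.0% or 75.3%.
- Start-up lag of 1, 2 or 3 months: 71.7%, 69.6% or 67.4%.

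**7. Power, as an indication only.** The protocol's equation did not survive in the text, so I assume the usual pair-matched form, with two pairs deducted: z = √[(6 − 2) d²/V] − 1.96, where V = [p0(1 − p0) + p1(1 − p1)]/n + k²(p0² + p1²).
- Whole sample, n = 180, 47.8% v 61.4%: V = 0.4865/180 + 0.0625 × 0.6055 = 0.0405; √(4 × 0.0185/0.0405) = 1.35; z = −0.61; power about 27%.
- Births after the start, n = 90, 47.8% v 75%: V = 0.4370/90 + 0.0625 × 0.7910 = 0.0543; √(4 × 0.0740/0.0543) = 2.33; z = 0.37; power about 65%.

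With 95 women per cluster, about 47 of them exposed, the same formula gives about 26% and 61%. Without deducting two pairs, the figures at 180 and 90 are about 38% and 82%. Restriction wins each time, because between-cluster variation dominates V and halving n costs little. The comparison holds k equal in both samples. It is not a check of the protocol's sample sizes.

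**The case against.** The strongest reply is that the protocol never ties the target to this sample. The target speaks of what mothers will do for the newborn, which can be read as births still to come. No item in section 3.7 names colostrum, and the 24-hour recall captures current feeding. The months in section 3.7 have no stated origin, section 3.6 lists weight and height at 6 and 12 months, and section 5 plans repeated measurements on individuals, so a birth cohort is a possible reading. Under it the ceiling disappears. Denominators of process indicators are also often left to an analysis plan.

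Part of this stands: the link from target to sample and survey date is an inference. But section 3.5 defines the women by the age of a living child at the survey and does not describe a birth cohort. If the repeated measurements meant returning to women enrolled before training about the same child, no index birth would be exposed at all. Since plausible readings run from no dilution to total dilution, the objective itself needs the birth window.

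A reader might infer that 75% cannot be reached even with perfect uptake, so that the trial must report failure on it. The documents do not support that for the under-24-month sample. The miss is 1.1 points, rests on uniform ages and an exact 12-month survey, and vanishes under the small changes in step 6. The far lower 58.2% belongs to the 0-59 month criterion, which section 3.5 replaces.

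A reader might also extend the ceiling to the 60% exclusive-breastfeeding target. That does not follow. Infants under 6 months at a 12-month survey were all born after training, and the protocol gives no baseline exclusive-breastfeeding rate from which to compute a ceiling.

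**Conclusion.** The point holds for colostrum and the other birth-time practices, as a matter of dilution. With the under-24-month sample, a survey about 12 months after training and roughly uniform ages, about half the answers are fixed beforehand and the visible effect is about half the true one: 13.6 points instead of 27.2. The target is then practically out of reach at a ceiling of about 74%. A start-up lag would worsen this; a slightly later survey, or reporting on the youngest child, would ease it.

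The reach is limited. These are process targets and part of a secondary outcome. The caregivers' principal comparison is a knowledge score, and the primary outcomes are growth and acute malnutrition; neither is affected by this argument. The change is worth making because it is cheap and improves the comparison.

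**What to change.** In the Targets, in section 3.5 (caregivers) and in section 3.6, state that colostrum and the other birth-time practices are assessed only in mothers whose index child, defined as the youngest, was born after the intervention start. Define that start as one calendar date per pair, applied to both the intervention and the control centre so that the arms have the same birth window. The protocol does not yet define such a date, so it must be added. Use the last survey round for the target.

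For exclusive breastfeeding, state only that it is assessed in infants under 6 months at the survey, which the planned 24-hour recall allows.

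The cost is wording; child age is already needed for eligibility and anthropometry. The drawback is that birth-time indicators rest on about half the sampled mothers, about 90 of 180 per cluster. In the indicative calculation that still gives more power than the diluted full sample.
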